## Abstract

Polycystic ovary syndrome (PCOS) is a common endocrine condition in reproductive-aged women associated with metabolic, reproductive and psychological features. Lifestyle modification (diet/physical activity) is considered first-line treatment for PCOS. However, there is limited high-quality evidence to support therapeutic dietary interventions for PCOS beyond general population-based healthy eating guidelines. Adherence to a Mediterranean diet (MedDiet), with or without energy restriction, improves cardiometabolic health in populations including persons with or at high risk of cardiovascular disease and type 2 diabetes. However, there is limited research examining the MedDiet in PCOS. Therefore, this 12 week randomized controlled trial will investigate the efficacy of a MedDiet on cardiometabolic and hormonal parameters and explore its acceptability and feasibility in PCOS. Forty-two overweight and obese women with PCOS (aged 18–45 years) will be randomized to receive dietary advice consistent with Australian Dietary Guidelines or an ad libitum MedDiet intervention. All participants will receive fortnightly counselling to facilitate behaviour change. The primary outcomes will be changes in insulin resistance, glucose, total testosterone and sex hormone-binding globulin. Secondary outcomes include changes in body weight and feasibility and acceptability of the MedDiet intervention. The results of this study will provide further evidence on specific dietary approaches for management of PCOS.

## 1. Introduction

Polycystic ovary syndrome (PCOS) is a common endocrine condition associated with reproductive, metabolic and psychological features [1]. This condition affects women of reproductive age, with a prevalence of 6–18% depending on the diagnostic criteria used and population studied [2,3,4,5]. The European Society for Human Reproduction and Embryology/American Society for Reproductive Medicine (ESHRE/ASRM) international consensus workshop group has expanded the diagnostic criteria for PCOS to the Rotterdam criteria, which is based on women presenting with two of the three following criteria: (1) menstrual irregularity (infrequent menstrual periods) and/or anovulation; (2) clinical and/or biochemical hyperandrogenism; (3) polycystic ovaries based on ultrasound examination [6]. PCOS is underpinned by intrinsic insulin resistance (IR) that, in turn, worsens hormonal and clinical features including hyperandrogenism, hirsutism, oligo-/anovulation and polycystic ovarian morphology [1,7,8]. Infertility is also a clinical feature of PCOS, with up to 75% of these women suffering infertility due to anovulation [9]. Moreover, women with PCOS may experience higher levels of stress, depression and anxiety, which negatively impacts on health-related quality of life and self-efficacy [10,11,12]. For instance, there is evidence to support a higher prevalence of disordered eating behaviours and poor body image amongst women with PCOS, which subsequently contributes to adverse mental health outcomes, including symptoms of depression and anxiety [13,14,15].

Women with PCOS also experience higher levels of weight gain and greater prevalence of overweight and obesity and central obesity, compared to women without PCOS, which exacerbates IR [16,17,18]. As such, this combination of cardiometabolic risk factors substantially increases the risk for cardiovascular disease (CVD), metabolic syndrome and type 2 diabetes mellitus (T2DM) in PCOS [8,19,20]. Weight loss, in turn, improves all clinical features of PCOS [21]. Therefore, lifestyle modifications including adopting a healthy diet and regular physical activity are considered first-line treatment for both weight management (prevention of weight gain, modest weight loss and maintenance of weight loss) and to better manage health outcomes including cardiometabolic disease risk [22]. However, the optimal dietary approach as part of lifestyle management in PCOS remains controversial, with limited high-quality evidence to support any specific dietary approach for PCOS beyond general population-based guidelines from international evidence-based guidelines and recommendations and systematic reviews [23,24,25]. As such, dietary interventions which promote healthy long-term behaviour change, without necessarily focusing on weight loss and caloric restriction, may assist in improving distorted eating behaviours and preserve psychological health [26], which may indeed facilitate adherence and maintenance to longer-term lifestyle and behavioural change. Therefore, defining the optimal dietary approach, either with or without the need for caloric restriction, as a potential therapeutic intervention for the management of cardiometabolic outcomes in PCOS is of clinical interest. 

The MedDiet is a dietary pattern based on the cultural and dietary behaviours of the olive-growing regions of the Mediterranean basin before the mid-1960s [27,28]. Despite being referred to as a ‘diet’, in reality, the MedDiet is more correctly identified as a whole lifestyle approach which also incorporates time-honoured behavioural practices related to food consumption, including harvesting, traditional culinary techniques, frugality and conviviality [27,29]. While there is no single MedDiet, in the research literature, the MedDiet is often described predominately as a plant-based dietary pattern, consistent with a high intake of vegetables, fruits, nuts, legumes, unprocessed cereals, and daily use of extra virgin olive oil (EVOO) incorporated into all meals; moderate consumption of fish, shellfish, fermented dairy products (cheese and yoghurt) and wine (typically during meals); low or infrequent consumption of meat and meat products, processed cereals, sweets, vegetable oils, and butter [30,31]. Being predominately plant-based, the MedDiet is naturally low in saturated fat, and rich in several functional components, including vitamins and minerals, carotenoids, unsaturated fatty acids, and phenolic compounds, depicted by antioxidant and anti-inflammatory properties [32,33,34]. Therefore, the potential mechanistic benefits of the MedDiet on improving clinical features of PCOS may indeed be related to the anti-inflammatory potential of the dietary pattern, reductions in oxidative stress and a higher intake of antioxidants. Moreover, many core foods consistent with a MedDiet pattern (in particular vegetables, legumes, wholegrains, nuts and seeds) naturally have a low glycemic index (GI), which may lower the glycemic response or glycemic load (GL) of the diet [35]. As such, low GI/GL dietary patterns may be beneficial in PCOS through their role in regulating glucose metabolism, and in particular IR [36,37].

Previous clinical trials adopting a Mediterranean diet (MedDiet), with or without caloric restriction, have shown promising results for improving cardiometabolic health parameters in vulnerable populations, including those with or at risk of CVD [38] and T2DM [30,39]. In particular, adherence to a MedDiet affords protection against IR and improves glycemic control, particularly in patients with metabolic perturbations [40,41]. Furthermore, adherence to a MedDiet is inversely associated with central obesity in epidemiological studies and is associated with weight loss in dietary interventions [42,43]. Importantly, many of these benefits are independent of caloric restriction and weight loss due to the large number of functional foods and nutraceuticals present within the dietary pattern.

However, efficacy studies on the MedDiet for the management of PCOS using well-designed and robust clinical trials are scant. Using data from the Australian Longitudinal Study on Women’s Health (ALSWH), Moran et al. [44] reported that women with PCOS were more likely to consume a dietary pattern consistent with principles of a MedDiet, suggesting acceptability of a MedDiet in PCOS. Nevertheless, feasibility and acceptability studies exploring the adherence to a MedDiet are yet to be investigated in women with PCOS and warrant future exploration.

The primary aim of this study is to investigate the efficacy of a MedDiet on hormonal, metabolic and anthropometric measures, without caloric restriction, in overweight and obese women with PCOS. As a secondary aim of the proposed study, we will also explore the acceptability and feasibility of a MedDiet intervention in this same cohort of women.

## 2. Materials and Methods

### 2.1. Study Design, Participants and Recruitment

This study will be a randomized controlled trial (RCT) conducted over 12 weeks, at the University of the Sunshine Coast clinic spaces within the High-Performance Centre. English-speaking participants aged between ≥18 and ≤45 years who are overweight (≥25 kg/m^2^) or obese (≥30 kg/m^2^) with a confirmed diagnosis of PCOS (provided by a medical practitioner) in accordance with the ESRHE/ASRM diagnostic criteria will be eligible to participate. Participants will be recruited throughout Queensland, Australia via local flyers, newspaper advertisements, women’s health and GP clinics, and social media platforms including Facebook, Instagram and Twitter. Recruitment is expected to occur from June 2021 until June 2022. Volunteers who express interest will be screened for eligibility based on the inclusion and exclusion criteria outlined in Table 1. If eligible, volunteers will be invited to participate and will be provided with the research project information sheet and a 4 day food record provided by post or email. At the baseline assessment, participants will be required to provide informed consent prior to the collection of data. 

Participants will be recruited via a rolling recruitment strategy, where they will be randomized to receive either a standard healthy eating (HE) dietary approach consistent with the Australian Dietary Guidelines or a Mediterranean diet (MedDiet) intervention. Allocation will be stratified by BMI (25–29.9 kg/m^2^; ≥30 kg/m^2^) using a random number, computer-generated randomization schedule developed and managed by an independent member of the research team. Participants will attend the clinic for baseline and week 12 assessments and receive fortnightly counselling sessions thereafter for the duration of the study. Participants will be required to attend in-person appointments for the baseline and week 12 assessments, but will be offered the choice of in-person or online consultations for weeks 2, 4, 6, 8 and 10. An overview of the recruitment method, randomization process and study schedule is provided in Figure 1. 

### 2.2. Data Collection

The timeframe for this study will be 15 months, from June 2021 until September 2022. Activities completed in this time include participant recruitment, data collection and data analysis. Outcome measures (primary or secondary) will be assessed at baseline and week 12. The primary outcome measures for this study include biochemical and hormonal parameters including fasting insulin, glucose, total testosterone and sex hormone-binding globulin (SHBG). Secondary outcomes include body weight, waist circumference and the feasibility and adherence to the MedDiet intervention. Adherence to the dietary intervention will be evaluated using dietary checklists, 3 separate 4 day food records (see dietary intervention below) and the MEDAS (see adherence to a MedDiet below).

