## 3. Analyses of Results

All continuous variables will be presented as the mean (±SD) or the median (IQR) with categorical variables presented as frequencies or percentages. For the efficacy component of the study, paired *t*-tests will be used to identify whether outcome measures change over time. After adjusting for potential covariates, analysis of covariance (ANCOVA) will be applied to identify differences between diet groups over time, with the dietary groups as the independent variable and outcome parameters (primary and secondary outcomes) as the dependent variable. All quantitative analyses will be performed using Statistical Package for the Social Sciences (SPSS) for Windows 26.0 software (IBM Corp., Armonk, NY, USA), with statistical significance set at *p* ≤ 0.05. Primary analyses will be carried out with results analysed based on the “intention to treat” protocol. The required sample size for the proposed study is powered based on change in HOMA-IR (primary outcome of the study) as reported by Ryan et al. [71]. For the proposed study, it was estimated that a total of *n*  =  32 participants would provide 80% power to detect a significant (*p*  <  0.05, 2-sided) change in HOMA-IR by 1.7 ± 0.5. Assuming an attrition rate of 30%, the target sample size for the proposed study will be *n*  =  42 participants (MedDiet intervention *n* = 21; HE dietary approach *n* = 21).

For the acceptability and feasibility component of the study, all semi-structured interviews will be audio-recorded and transcribed verbatim. Data will be analysed through open coding, whereby codes will be iteratively revised and deductively clustered into subthemes and themes according to the framework technique proposed by Richie et al. [72]. These themes will then be mapped against the COM-B constructs. All participant interviews, coding and theme development will be performed by NS. To ensure reliability, successive 10% of the transcripts will be independently coded by another member of the research team until consistent coding occurs. In the event of discrepancies, coded transcripts will be discussed and recoded until a consensus is reached. Analyses of qualitative data will be performed using NVIVO software (QSR International, Melbourne, Australia), version 12.

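### The primary outcome is stated inconsistently: Section 3 names and powers change in HOMA-IR alone, while the Abstract and Section 2.2 each list four primaries, all tested at 0.05 with no order among them

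*Protocol article*

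**What the plan says.** Three places in the protocol article identify the primary outcome.

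- **Abstract:** "The primary outcomes will be changes in insulin resistance, glucose, total testosterone and sex hormone-binding globulin". This is four outcomes, the first being insulin resistance.
- **Section 2.2 (Data Collection):** "The primary outcome measures for this study include biochemical and hormonal parameters including fasting insulin, glucose, total testosterone and sex hormone-binding globulin (SHBG"). This is again four, but the first is fasting insulin. Neither HOMA-IR nor insulin resistance is named. Body weight and waist circumference are placed among the secondary outcomes.
- **Section 3 (Analyses of Results):** the sample size is "powered based on change in HOMA-IR (primary outcome of the study"). This is one outcome, in the singular, and no other outcome has a power statement.

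Section 2.3 defines the HOMA index as fasting insulin times fasting glucose divided by 22.5. It is the only index of its kind in the article.

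On testing, Section 3 applies ANCOVA between the diet groups to both primary and secondary outcomes, and paired t-tests to change over time. All quantitative analyses are run "with statistical significance set at *p* ≤ 0.05". The text gives no order among the primaries, no split of alpha and no statement of which result would make the trial positive.

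**The concern.** A trial's primary outcome settles two things before data are seen: which comparison decides efficacy, and which comparison the sample size is meant to serve. Here the outcome that sets the sample size is missing from the section that defines the outcomes, and two of the three statements give four primaries where the third gives one.

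A team following the article could in good faith report HOMA-IR as decisive, or any of the four listed variables, and cite a section in support. If the choice is made after the results are known, the 5% level of a single test no longer describes the error rate of the efficacy claim. Three of the listed primaries (glucose, total testosterone and SHBG) would also carry primary status with no stated power.

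**Working it through.** **1. The three statements side by side**

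| Variable | Abstract | Section 2.2 | Section 3 |
|---|---|---|---|
| HOMA-IR / insulin resistance | primary | not listed | sole primary, powered |
| Fasting insulin | not listed | primary | not named |
| Glucose | primary | primary | not named |
| Total testosterone | primary | primary | not named |
| SHBG | primary | primary | not named |

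Under the Section 2.3 formula, fasting insulin and HOMA-IR are related but distinct variables, because HOMA-IR also varies with glucose. The Abstract's insulin resistance is most naturally HOMA-IR. That leaves two conflicts: one primary against four, and fasting insulin in place of HOMA-IR in Section 2.2.

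**2. Error rate, if any one of k primaries sufficed**

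Inputs: 0.05 per test (Section 3) and k = 4 (Abstract or Section 2.2). The any-one rule and the correlations are assumptions, since the article gives neither.

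- Independent outcomes: 1 − 0.95^4 = 1 − 0.8145 = 0.185.
- Equally correlated normal test statistics, simulated (300,000 draws, two-sided 0.05):

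| Assumed common correlation | Chance of at least one false positive, k = 4 |
|---|---|
| 0 | 18.5% |
| 0.3 | 17.4% |
| 0.5 | 15.6% |
| 0.7 | 13.1% |
| 0.9 | 9.3% |

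If HOMA-IR is added to the Section 2.2 list, k = 5 and the independent figure is 1 − 0.95^5 = 0.226.

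**3. The plan's own power figure**

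Section 3 states 32 participants, 80% power, two-sided 0.05 and a change of 1.7 ± 0.5. Reading these as a between-group difference of 1.7 with SD 0.5, the normal formula gives

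n per arm = 2 × (1.960 + 0.842)² × (0.5/1.7)² = 1.36, rounded up to 2.

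The stated 32 (16 per arm) is therefore not reproduced on that reading. The article does not say whether 0.5 is an SD or an SE, or whether the change is within or between groups. The next step therefore takes the stated 80% at 16 per arm at face value and solves for the effect that yields it: standardised difference d = 1.024 by t-test, or (1.960 + 0.842) × √(2/16) = 0.990 by the normal approximation.

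**4. Power if four primaries were kept under Bonferroni**

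The adjusted alpha is 0.05/4 = 0.0125.

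- t-test, d = 1.024, 16 per arm: power 59.7%.
- Normal approximation, d = 0.990: Φ(2.802 − 2.498) = Φ(0.304) = 61.9%.
- Restoring 80% at that effect: 23 per arm, 46 evaluable, and 46/(1 − 0.30) = 65.7, so 66 enrolled, against the stated target of 42.

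With HOMA-IR as the single primary, alpha stays at 0.05 and the sample size does not change on this account.

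**The case against.** The strongest reply has four parts.

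- **The article never says co-primary and gives no rule that one success is enough.** This stands. If all four had to succeed, the type I error would not be inflated at all. A reader might infer that a positive trial can be claimed on any one outcome, or that the family-wise error rate is 18.5%. The text does not prevent the first, but it states neither, and it nowhere promises a family-wise rate of 5%.
- **Multiplicity handling is commonly left to a statistical analysis plan, and this is a condensed article.** This also stands: the lack of an adjustment is not by itself the defect. It does not remove the contradiction, because any later plan would have to overrule at least one of the three statements.
- **The naming differences are smaller than they look.** This stands in part. The powered variable is in the Abstract's list, given Section 2.3, and Section 2.2 uses open wording and covers both components of HOMA. The article therefore does not contain three wholly rival definitions. One primary against four remains, as does the absence of HOMA-IR from Section 2.2.
- **The study calls itself small and its evidence preliminary (Section 4).** This lowers the stakes. But Section 4 also expects the findings to offer an evidence-based approach and to feed into international guidelines, so the deciding outcome still needs to be fixed.

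A reader might also infer a further contradiction from the primary aim in the Introduction, "to investigate the efficacy of a MedDiet on hormonal, metabolic and anthropometric measures", since it includes anthropometry. The text does not support that: an aim may span primary and secondary outcomes, and Section 2.2 plainly ranks weight and waist as secondary.

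**Conclusion.** The inconsistency is in the current text and does not depend on anything left to another document. Section 3 has a single primary and powers only that; the Abstract and Section 2.2 have four, and Section 2.2 leaves out the powered variable. With every outcome tested at the same threshold and none ranked, the plan as written leaves the deciding endpoint open.

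The size of the problem is conditional. The range of about 9% to 18.5% assumes an any-one-wins rule, four outcomes, and a common correlation between 0.9 and 0. The article supplies no correlations, and glucose and HOMA-IR are linked by construction, so the independent figure is the upper end of that range. The power of about 60% rests on an effect solved back from the stated 80% and not on 1.7 ± 0.5. Taken as difference and SD, those figures would give power above 99.9% at 16 per arm even at alpha 0.0125. The 60% therefore shows what an adjustment would cost if the stated 80% is right; it is not a prediction for this trial.

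**What to change.** Name the between-group difference (MedDiet against HE) in change in HOMA-IR from baseline to week 12 as the sole primary outcome, in the same words in the Abstract, Section 2.2 and Section 3. This matches the sponsor's own basis for the sample size. List fasting insulin, glucose, total testosterone and SHBG as secondary outcomes, reported with 95% confidence intervals and without a confirmatory claim.

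The text edits are short and add no participants on this account. The real cost is that glucose, total testosterone and SHBG lose primary status. Section 2.1 expects recruitment from June 2021, so this change of outcome status should be dated, recorded, and made without sight of between-group results.

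Keeping several primaries is a legitimate alternative. The sponsor would then need to list them identically in all three places, state the multiplicity procedure and what counts as success, and restate the power at the adjusted alpha: about 60% under Bonferroni at 16 per arm, or about 66 enrolled to recover 80%, on the back-solved effect used above.

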### 2.3. Biochemical Assessments

After a 12 h overnight fast, participants will be required to provide a venous blood sample collected by a trained phlebotomist at a local Queensland Medical Laboratory (QML) pathology site. Blood samples will be collected at baseline and week 12. Participants will receive a QML blood request form at the baseline and week 12 assessments and instructed to attend a QML pathology collection site immediately following the assessment. Biochemical assessments will include total testosterone, sex hormone-binding globulin, fasting insulin and fasting glucose. Serum concentrations of these biochemical parameters will be collected using blood collection tubes with no additives and allowed to clot at room temperature for 30 min. The homeostatic model assessment (HOMA) will be used as a surrogate measure from which to calculate insulin sensitivity according to the following equation:

Insulin sensitivity = [fasting insulin (mU/L) × fasting glucose (mmol/L)]/22.5 [45].

Analysis of all serum biochemical parameters will be conducted at a local QML pathology laboratory.

### 2.4. Anthrompometry and Body Composition

A calibrated digital scale (AND Weighing; HW-KGL, Melbourne, Australia) will be used to record body mass (without footwear and heavy clothing) to the nearest 0.1 kg. Height will be measured to the nearest 0.1 cm whilst barefoot using a wall-mounted stadiometer (Holtain Limited, Crymych, UK). BMI will be calculated as weight (kg) divided by the square of height (m^2^). Waist circumference will be performed by trained research personnel and measured to the nearest 0.1 cm using a flexible steel tape measure (Lufkin Executive Thinline) at the point midway between the iliac crest and the lower costal border (lower rib) according to standardized protocols. This will be measured in triplicate with the mean of the three measures used for the final analyses. Body weight will be collected at baseline and week 12 and monitored fortnightly throughout the duration of the study. Waist circumference will be assessed at baseline and week 12.

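### Fortnightly body weights are given no role in the planned week-12 weight comparison, although 30% attrition is expected and a baseline-adjusted longitudinal model could use them

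*Protocol article*

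**What the plan says.** Section 2.2 names weight as an outcome: "Secondary outcomes include body weight, waist circumference and the feasibility and adherence to the MedDiet intervention". The same section sets the timing for all outcomes: "Outcome measures (primary or secondary) will be assessed at baseline and week 12". Section 2.4 adds a denser schedule for weight alone: "Body weight will be collected at baseline and week 12 and monitored fortnightly throughout the duration of the study". It also describes a calibrated digital scale that "will be used to record body mass (without footwear and heavy clothing) to the nearest 0.1 kg".

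Section 2.1 places counselling sessions between the two clinic assessments, at which participants "will be offered the choice of in-person or online consultations for weeks 2, 4, 6, 8 and 10". No section says how weight is obtained when a session is online.

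Section 3 gives the methods for primary and secondary outcomes. Paired t-tests "will be used to identify whether outcome measures change over time", and "analysis of covariance (ANCOVA) will be applied to identify differences between diet groups over time". It also states: "Primary analyses will be carried out with results analysed based on the “intention to treat” protocol". The target is 42 women, 21 per arm, with 30% attrition assumed. Allocation is stratified by BMI (section 2.1).

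**The concern.** The schedule yields up to seven weights per woman (weeks 0, 2, 4, 6, 8, 10 and 12), but the outcome timing and named tests use two. Neither a paired t-test nor an ANCOVA with one outcome value per woman has a place for the weights in between.

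With complete follow-up this would cost little, since the week-12 weight would be known for every woman. The plan expects otherwise. A woman who leaves after week 6 may have three post-baseline weights, yet an ANCOVA on observed week-12 weights takes nothing from her.

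Two things are at stake. One is precision in a small trial. The other is bias: if women whose weight is not responding leave more often, the completers in each arm are a selected group, and the fortnightly weights are the data that would show this and largely correct it. Weight is well placed for such a repair, because waist circumference and the blood measures are taken only at baseline and week 12.

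**Working it through.** **The plan's own figures.** The documents state no sample size, SD or expected difference for weight; the power statement concerns HOMA-IR. So there is no weight figure to reproduce. What follows from the text:

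- Intermediate sessions: weeks 2, 4, 6, 8 and 10, which is 5.
- Women expected to have a week-12 weight: 42 × 0.7 = 29.4, or 14.7 per arm.
- Women expected to lack one: 42 × 0.3 = 12.6, about 13.

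**Ceiling on the precision gain.** If dropout is unrelated to weight, the variance of the adjusted week-12 difference is proportional to 1/n. Had all 42 women been weighed at week 12, it would be 14.7/21 = 0.70 of the completers' variance. Interim weights can recover at most this 30%.

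**Assumed values (none is in the documents).** 21 per arm; true diet difference -2 kg at week 12; between-woman SD 15 kg; individual 12-week trend SD 2, 3 or 4 kg; random walk with SD 1 kg at 12 weeks; measurement error SD 0.5 kg; about 30% dropout. The longitudinal model constrains the arms to equal means at baseline and takes the covariance as known, which is its best case.

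**Completer ANCOVA.** Given baseline, the week-12 variance is close to trend² + 1 + 0.25 + 0.25, and SE = √(2 × variance / 14.7):

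| Trend SD (kg) | Variance | SE (kg) |
|---|---|---|
| 2 | 5.5 | 0.87 |
| 3 | 10.5 | 1.20 |
| 4 | 17.5 | 1.54 |

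**Dropout unrelated to weight (simulation).** The ratio of longitudinal-model variance to completer-ANCOVA variance was 0.80, 0.75 and 0.74 for trend SD 2, 3 and 4. Repeat simulations of the same design gave ratios from 0.72 to 0.82. A ratio of 0.80 to 0.72 is 20 to 28% less variance, or an SE smaller by 1 - √0.80 = 11% to 1 - √0.72 = 15%. With an error SD of 1 kg (trend SD 3) the ratio was 0.81. With the interim-weight error alone raised to 1.5 kg it was 0.82.

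**A less favourable correlation.** Suppose instead an autoregressive correlation of 0.99 between adjacent visits, scaled by 0.999, with dropout spread evenly over the six intervals. The week-0 to week-12 correlation is 0.999 × 0.99^6 = 0.9405. The completer SE is √(2/14.7 × (1 - 0.9405²)) = 0.125 SD units, and the longitudinal model gives 0.116. That is a 7% smaller SE, or about 14% less variance.

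**Dropout driven by observed poor weight response (truth -2.00 kg).**

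| Trend SD (kg) | Completer ANCOVA | Longitudinal model |
|---|---|---|
| 2 | -1.66 | -2.02 |
| 3 | -1.49 | -2.02 |
| 4 | -1.34 | -2.07 |

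The completer estimate falls short by 0.34 to 0.66 kg, which is 17 to 33% of the assumed effect. The two variances were about equal here, so the gain is in bias. With milder dropout (21 to 27%) the ANCOVA gave -1.76, -1.60 and -1.41. With interim error of 1.5 kg (trend SD 3) it was -1.55 against -2.03. A 1 kg person-specific offset in remote weights left the longitudinal estimate near -2.0. In these runs 81 to 91% of early leavers had at least one post-baseline weight.

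**A version of the model to avoid.** Visit, diet and diet-by-visit fitted to weeks 0 to 12 with free baseline means, and the raw week-12 contrast read off, loses the baseline adjustment. Its SE is at least 15 × √(2/21) = 4.63 kg. Simulation gave about 4.6 to 5.0 kg, against 0.8 to 1.5 kg for the planned ANCOVA.

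**The case against.** A reader might infer that the plan discards the fortnightly weights and drops every woman who leaves early from the weight comparison. The documents do not say either. Section 3 names no complete-case rule and declares intention to treat for the primary analyses. How missing values are handled is commonly left by an article to the full protocol or analysis plan, so that silence is not the point here. Exclusion follows only if the ANCOVA is run on observed week-12 weights.

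The schedule is also internally consistent. Section 2.4 separates collecting weight at two times from monitoring it fortnightly. The two outcome times are the in-person assessments, and ANCOVA on a week-12 value is a standard, valid method. Interim weights may come from online sessions, and participants choose the mode themselves, so a term for mode would not fully remove a difference between scales. Keeping the outcome to clinic weights can be defended.

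The magnitudes rest on assumptions. A response-driven dropout mechanism is less obvious in a trial that prescribes no energy restriction in either arm (section 2.9). An unstructured covariance for seven visits has 7 × 8 / 2 = 28 parameters, too many to estimate well from 42 women.

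All of this limits the size and tone of the point. It does not change the fact that the stated outcome times and named methods give already planned measurements no role, nor that noisier interim weights still helped in the checks.

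**Conclusion.** The point holds as a recommended improvement to a secondary analysis. It is not an error that invalidates the planned one. As written, the weight comparison uses baseline and week 12 only, while five further weights per woman are planned and about 13 of 42 women are expected to lack the final one.

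If the ANCOVA uses observed week-12 weights, the loss is roughly 20 to 28% in variance under unrelated dropout with woman-specific trends, and about 14% under an autoregressive correlation. It is less again once the covariance has to be estimated. If leaving depends on observed weight response, the completer estimate can be short by about 0.3 to 0.7 kg of an assumed 2 kg. These figures depend on assumed SDs, dropout timing and dropout mechanism. The text establishes the mismatch, not its size. The primary outcomes are unaffected.

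**What to change.** Keep the week-12 diet difference as the target and estimate it from all available weights in a baseline-adjusted longitudinal model. Two forms are suitable:

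- baseline weight as one of the outcomes, with the arm means constrained to be equal at week 0; or
- post-baseline weights as outcomes, with baseline weight as a covariate.

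In either form include visit, diet-by-visit and BMI stratum, and specify a parsimonious covariance in advance, because only 42 women are enrolled. Do not report an unconstrained raw week-12 contrast.

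Reconcile sections 2.1 and 2.4 by stating how weight is obtained in online weeks. Record for each interim weight whether it came from the clinic scale or was obtained remotely, and repeat the analysis with clinic-scale weights only.

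The cost is a paragraph of analysis wording and one data field, with no added visits or participants. Two limits remain. Remote weights may be noisier or offset, which the clinic-scale analysis would help to show. Women who leave before week 2 contribute only their baseline weight.
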